# The SPARK Study: a phase II randomized blinded controlled trial of the effect of furosemide in critically ill patients with early acute kidney injury

**DOI:** 10.1186/1745-6215-11-50

**Published:** 2010-05-11

## Abstract

**Background:**

Furosemide is commonly prescribed in critically ill patients with acute kidney injury (AKI). Existing data from observational studies and small clinical trials have significant limitations and have reported conflicting findings. There remains controversy on whether furosemide can impact clinical outcomes in critically ill patients with AKI; however, a survey of intensivists and nephrologists showed equipoise for high-quality evidence on this important issue.

**Design/Methods:**

This protocol summarizes the rationale and design of a phase II randomized, blinded, placebo-controlled trial of a low-dose continuous infusion of furosemide, titrated to the physiology parameter of urine output, in critically ill patients with early AKI. Two hundred sixteen adult critically ill patients with early evidence of AKI, defined by the RIFLE criteria, will be enrolled. Included patients will also have fulfilled ≥2 criteria of the systemic inflammatory response syndrome and achieved immediate goals of acute resuscitation. The primary outcome is progression in severity of kidney injury. Secondary outcomes include: safety, fluid balance, electrolyte balance, the need for renal replacement therapy, duration of AKI, rate of renal recovery, mortality and changes in novel serum and urine biomarkers of AKI. The primary analysis will be intention-to-treat. Planned recruitment will be complete by June 2011 and results available by December 2011.

**Trial Registration:**

ClinicalTrials.gov Identifier NCT00978354

## Background

Acute kidney injury (AKI) is common and increasingly encountered in hospitalized patients [1-3]. An estimated 6% of critically ill patients admitted to intensive care (ICU) develop severe AKI, and approximately 70% eventually receive acute renal replacement therapy (RRT)[4]. Moreover, critical illness complicated by AKI remains associated with high morbidity, mortality and health resource use [4-11].

There are few, if any, interventions proven to impact on the clinical course and outcome for critically ill patients once AKI is established[12,13]. However, important questions remain regarding the supportive role of selected interventions that still demand higher-quality evidence and better characterization in randomized trials to evaluate their impact in AKI. One example is: what is the role for loop diuretics, specifically furosemide, in the management of critically ill patients with early AKI?

Furosemide acts at the medullary thick ascending loop of Henle to inhibit the Na+/K+/Cl- pump on the luminal cell membrane surface and can theoretically reduce renal tubular oxygen demand[14,15]. Experimental data have also suggested low-dose furosemide infusion may attenuate ischemia/reperfusion-induced apoptosis and associated gene transcription in AKI[16,17]. These data support the hypothesis that the timely administration of furosemide may attenuate and/or reduce the severity of early onset AKI. In addition, furosemide may also have an important adjuvant role for maintaining fluid homeostasis and for optimal delivery of nutrition in critically ill AKI patients[18,19].

Furosemide remains the most common loop diuretic prescribed in critically ill patients[20]. In the BEST Kidney Study, a large multi-centre observational study of >1700 critically ill patients with AKI, 70% had received diuretics at the time of enrollment, of whom 98% were receiving furosemide[21]. While numerous studies have evaluated loop diuretics in the treatment of AKI [22-30], the majority have failed to find consistent clinical benefit. Moreover, two large observational studies of AKI in critically ill patients have reported discrepant findings on the effect of loop diuretics on mortality and renal recovery[21,31]. Additional small trials have suggested that diuretics may reduce the severity of kidney injury by converting "oliguric" to "non-oliguric" AKI, shorten the duration of AKI, improve the rate of renal recovery, and perhaps delay or ameliorate need for RRT [22,24,32-35]. However, improvements in survival or renal recovery have yet to be confirmed with high-quality evidence. Accordingly, there is controversy as to whether furosemide can impact clinical outcomes and should be used in critically ill patients with AKI [36-40].

A recent systematic review of randomized trials assessing the role of loop diuretics in AKI found five trials enrolling 555 patients that focused on critically ill patients[41]. This review found no statistical difference in mortality (odds ratio [OR], 1.28, p = 0.18) or renal recovery (OR, 0.88, p = 0.5) for use of loop diuretics compared with control. However, loop diuretics were associated with a shorter duration of RRT (weighted mean difference, -1.4 days, p = 0.02), shorter time to spontaneous decline in serum creatinine (weighted mean difference, -2.1 days, p = 0.01) and a greater increase in urine output from baseline (OR, 2.6, p = 0.004). There was insufficient data to comment on the impact of loop diuretics on electrolyte abnormalities, fluid balance, duration of mechanical ventilation, secondary organ dysfunction, hospital length of stay or health costs.

Importantly, however, this review found that the overall trial quality and applicability of this evidence to critically ill patients was poor[41]. For example, trials were generally small, confounded by co-interventions (i.e. mannitol, dopamine), and characterized by delayed or late intervention (i.e. prolonged periods of oligo-anuria or already receiving RRT at the time of enrollment). Finally, these trials often administered furosemide as large intravenous bolus doses with no specific titration of therapy to physiologic endpoints such as urine output. As a consequence, these data have limited applicability to modern critically ill patients and to current ICU practice.

A recent multi-national survey of intensivists and nephrologists showed that most respondents did not believe that furosemide use in AKI would directly improve outcomes such as mortality, need for RRT, or renal recovery[20]. However, there was significant uncertainty about the existing evidence and the majority had equipoise for and supported a trial on this issue. Accordingly, we have proposed a phase II randomized, blinded, placebo-controlled trial of a furosemide infusion titrated to urine output in critically ill patients with early AKI.

## Objectives

The specific objectives of this trial are:

• To compare the efficacy and safety of a continuous infusion of furosemide versus placebo titrated to the physiology parameter of urine output in early AKI on the primary outcome of progression in severity of kidney injury from early AKI.

• To evaluate the impact of furosemide versus placebo on key secondary endpoints including: fluid balance; electrolyte and acid-base balance; the need for RRT; total duration of AKI; the rate of renal recovery; and mortality.

• To evaluate the impact of furosemide versus placebo on the tertiary endpoint of differences, trajectory and prognostic value of novel serum and urine biomarkers for AKI.

## Design/Methods

### Study Design, Setting and Patient Population

This is a phase II randomized, blinded, placebo-controlled trial of ICU patients with early AKI with randomization stratified by sepsis. This study will be performed at the University of Alberta Hospital (UAH) General Systems Intensive Care Unit (GSICU). The UAH is an academic/tertiary care hospital and regional trauma centre with approximately 1300-1400 annual admissions. All patients admitted to the GSICU will be screened for eligibility.

### Operational Definitions

#### Acute kidney injury (AKI)

The operational definition for early AKI will be defined and classified according to a modified RIFLE criteria (acronym indicating Risk of renal dysfunction; Injury to the kidney; Failure of kidney function; Loss of kidney function; and End-stage kidney disease) as outlined by the ADQI Working Group [42]. In brief, the RIFLE criteria classifies AKI into three categories of severity (Risk, Injury, and Failure) and two categories of clinical outcome (Loss and End-stage kidney disease) based on relative changes to serum creatinine and urine output. The presence of early AKI will be defined by a minimum of *RIFLE class - RISK*: an abrupt (within 7 day) reduction in kidney function characterized by an relative increase in serum creatinine of ≥ 50% (1.5 fold) or an absolute increase of ≥ 26.5 μmol/L from baseline or a reduction in urine output of ≤ 0.5 mL/kg/hr for ≥ 6 hours. For reference, the RIFLE category INJURY is defined as a relative increase in serum creatinine ≥ 100% (2.0 fold) or a reduction in urine output of ≤ 0.5 mL/kg/hr for ≥ 12 hours. The RIFLE category FAILURE is defined as a relative increase in serum creatinine ≥ 200% (3.0 fold) or an absolute value ≥354 μmol/L (accompanied by an acute increase ≥44.2 μmol/L) or a reduction in urine output of ≤0.3 mL/kg/hr for ≥ 24 hours or anuria for ≥ 12 hours.

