### Inclusion Criteria

Patients must fulfill all of the following inclusion criteria:

• Peripheral or central intravenous catheter and urinary catheter

• Early AKI

• ≥ 2 criteria for the systemic inflammatory response syndrome (SIRS) within 24 hours

• Achieved immediate resuscitation goals (as directed by the treating physician) including fluid resuscitation AND/OR vasoactive therapy to achieve mean arterial pressure ≥65 mmHg, central venous pressure ≥8 cmH2O, central venous oxygen saturation ≥70% (if measured) AND/OR cardiac index ≥2.5 L/min/1.73 m^2 ^(if measured).

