### Exclusion criteria

The following conditions will lead to ineligibility for study entry:

• Age <18 years

• Confirmed or suspected pregnancy (verified by serum [β-HCG] pregnancy test if necessary)

• Obstructive etiology for AKI

• ≥ Stage 4 chronic kidney disease (defined by an estimated glomerular filtration rate <30 mL/min/1.73 m^2^), end stage kidney disease on chronic RRT, kidney transplantation or already received RRT in ICU

• Resolving AKI, defined as a ≥25% or ≥44.2 μmol/L decline from peak increase in serum creatinine

• Acute pulmonary edema requiring urgent use of furosemide or RRT or patient already receiving continuous furosemide infusion

• Patient is moribund with expected death within 24 hours

• Known or suspected drug allergy to furosemide

• Enrolled in concomitant randomized trial

• Prior enrollment in SPARK

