### Trial Protocol

#### Description of Study Flow

Figure 1 outlines the study flow. Patients will be identified in the ICU by daily surveillance by the research coordinator or when identified by the treating ICU physician. Each patient's eligibility will be verified by use of a one-page checklist that summarizes the inclusion and exclusion criteria. This checklist will be included in the standardized case-report form (CRF).

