### Sample Size Estimation

Our primary outcome measure for this trial is progression from early AKI (RIFLE class - **RISK**) to a more severe form of AKI, defined by progression in AKI to the development of either RIFLE class - **Injury or Failure**. Based on data from a large observational study, an estimated 60% of critically ill patients with early AKI worsen and develop further kidney injury[46]. We estimate that furosemide will contribute to a 20% absolute reduction in the proportion of those patients who progress from early AKI (RIFLE class - **RISK**) to either RIFLE class - **Injury or Failure**. This would require a total sample size of 214 patients and provide 80% power (alpha 0.05) for detection of a 20% difference in the proportion with progression of AKI. An estimated 50% of patients developing early AKI will have sepsis[47]. Randomization will be stratified by the presence of sepsis. The total sample size was increased to 216 patients to ensure a balanced number of patients in each treatment arm (Figure 1).

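### Early AKI has a floor (RIFLE RISK) but no ceiling, so patients already in INJURY or FAILURE can be randomised into a trial whose primary outcome is RISK progressing to INJURY or FAILURE

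*Protocol article*

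**What the plan says.** - **Definition (Protocol article, Acute kidney injury (AKI)).** "The presence of early AKI will be defined by a minimum of" RIFLE class RISK: a creatinine rise of at least 1.5-fold or at least 26.5 μmol/L, or urine output of 0.5 mL/kg/hr or less for at least 6 hours. The next class up is also given: "RIFLE category INJURY is defined as a relative increase in serum creatinine ≥ 100% (2.0 fold"), or the same low urine output for at least 12 hours. INJURY and FAILURE are described as reference points and not as limits on entry.
- **Inclusion Criteria.** "Patients must fulfill all of the following inclusion criteria"; early AKI is one of them, with no class stated.
- **Exclusion criteria.** "The following conditions will lead to ineligibility for study entry". The nearest items are stage 4 or worse chronic kidney disease, "end stage kidney disease on chronic RRT, kidney transplantation or already received RRT in ICU", and resolving AKI. INJURY or FAILURE at entry is not listed.
- **Sample Size Estimation.** "Our primary outcome measure for this trial is progression from early AKI", which is glossed there as RIFLE class RISK, to a more severe form, "defined by progression in AKI to the development of either RIFLE class" Injury or Failure. The 60% control rate is stated for early AKI and the 20-point reduction for that transition.
- **Statistical Analysis.** The primary outcome is compared by Fisher's exact test on an intention-to-treat basis.

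**The concern.** The population that can be enrolled is wider than the population for which the primary outcome is defined. Each higher RIFLE class contains the RISK criteria, so a patient in INJURY or FAILURE satisfies the entry definition. Under intention-to-treat that patient stays in the denominator, and the protocol does not say how to score him or her. Such a patient could be counted as an event (the end state is present) or as a non-event (no progression from RISK occurred). Two analysts following the text could therefore report different event rates from the same data. Patients whose outcome is settled at entry also add no information on treatment and dilute the difference that the sample size was built on.

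**Working it through.** **1. Does the definition admit the higher classes?**

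| Class | Creatinine route | Urine route | Meets RISK? |
|---|---|---|---|
| RISK | ≥1.5-fold or rise ≥26.5 μmol/L | ≤0.5 mL/kg/hr for ≥6 h | yes |
| INJURY | ≥2.0-fold | ≤0.5 mL/kg/hr for ≥12 h | yes: 2.0 > 1.5; 12 h > 6 h |
| FAILURE | ≥3.0-fold, or ≥354 μmol/L with rise ≥44.2 μmol/L | ≤0.3 mL/kg/hr for ≥24 h, or anuria ≥12 h | yes: 3.0 > 1.5; 44.2 > 26.5; less urine for longer |

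The exclusion for resolving AKI removes only patients whose creatinine is already falling from its peak. Worsening or stable INJURY or FAILURE remains eligible.

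**2. Can these patients have the outcome as defined?** FAILURE is the top of the three severity classes, so no further progression is possible. An INJURY patient can move to FAILURE, but not from RISK, and has already reached one of the two named end states. Counting that move would need a rule that the Sample Size Estimation section does not state.

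**3. Reproducing the planned sample size.** Inputs from Sample Size Estimation: 60% versus 40%, power 80%, alpha 0.05. Two-sided testing is stated in Statistical Analysis. Allocation is read as 1:1.

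n per arm = [1.960·√(2·0.5·0.5) + 0.842·√(0.6·0.4 + 0.4·0.6)]² / 0.2² = 96.9, that is 97.

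With the continuity correction: n′ = (n/4)·[1 + √(1 + 4/(n·0.2))]² = (96.9/4)·[1 + 1.098]² = 106.7, that is 107 per arm or **214 in total**, as stated. Exact Fisher power at 108 per arm (216) is 80.2%. The arithmetic is right when 60% versus 40% holds for everyone enrolled, and it leaves almost no reserve.

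**4. Worst-case dilution.** Let f be the share randomised in INJURY or FAILURE. The protocol gives no value, so f is an assumption. Suppose these patients contribute no treatment contrast.

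- Counted as events: f + (1−f)·0.6 versus f + (1−f)·0.4.
- Counted as non-events: (1−f)·0.6 versus (1−f)·0.4.

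Either way the difference is (1−f)·20 points. The two pairs of rates are complements of each other (for f = 10%, 1 − 0.64 = 0.36 and 1 − 0.46 = 0.54), so power is identical.

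| f (assumed) | Rates if events | Rates if non-events | Difference | Fisher power, 108 per arm | Total N for 80% (same formula) |
|---|---|---|---|---|---|
| 0 | 60% v 40% | 60% v 40% | 20 points | 80.2% | 214 |
| 10% | 64% v 46% | 54% v 36% | 18 points | 71.1% | 260 |
| 20% | 68% v 52% | 48% v 32% | 16 points | 62.1% | 318 |
| 30% | 72% v 58% | 42% v 28% | 14 points | 53.1% | 392 |

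**5. A milder handling.** If these patients were instead left out of the analysis, 97, 86 or 76 per arm would remain, with Fisher power of 76%, 72% or 62%. To keep 214 evaluable, 214/(1−f) = 238, 268 or 306 would have to be randomised. That handling would depart from the stated intention-to-treat analysis.

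**The case against.** **RISK-only intent.** The strongest reply is that the text can be read consistently. The Sample Size Estimation section twice ties early AKI to class RISK, the word early points the same way, and a stated minimum can be taken as a diagnostic threshold, with INJURY and FAILURE described only as the classes a patient may reach. A ceiling might also appear in the patient-flow figure, which is not reproduced, or on the eligibility checklist. The intent is plausible. But the gloss sits in the sample-size section and not among the entry criteria, and Description of Study Flow says the checklist summarises the printed inclusion and exclusion criteria, which contain no ceiling. The gloss therefore confirms that two stated rules disagree.

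**Stronger readings that the protocol does not support.**

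- *That such patients will be found often.* A reader might infer this because "Patients will be identified in the ICU by daily surveillance by the research coordinator", while the urine criterion moves from RISK to INJURY in 6 further hours. The same sentence gives a second route, identification by the treating physician; RISK can also be met through creatinine; and no class distribution at screening is given. Frequency is unknown.
- *That the outcome is fixed in both arms for every such patient.* The abstract and Objectives describe the outcome more loosely, as worsening severity. On that wording an INJURY patient could progress to FAILURE and could show a treatment effect. Only FAILURE at entry rules out further progression among the severity classes.
- *That the stated 80% power is lost.* The dilution figures need both an assumed share and zero contrast in all affected patients. If INJURY-to-FAILURE moves were counted and furosemide affected them, the loss would be smaller.

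**Conclusion.** The conflict is real and goes beyond missing detail: a stated eligibility rule with no upper class disagrees with a stated primary outcome and sample-size basis that start from RISK. Followed as written, the trial can randomise, and analyse by intention-to-treat, patients who already meet the end state, with no rule for scoring them. Confidence in this mismatch is high.

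Its size is conditional. The fall in power from 80% to about 71%, 62% or 53% is a worst case for assumed shares of 10%, 20% or 30% with no treatment contrast in those patients. The sample size of 214 is correct if entry is confined to RISK. The point needs resolving whatever the share turns out to be, because it decides who has the primary outcome, and a scoring rule chosen after unblinding would be post hoc.

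**What to change.** Reconcile the AKI definition, the Inclusion Criteria, the Exclusion criteria and the Sample Size Estimation section in one of two ways.

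1. **Preferred: limit entry to RIFLE RISK at randomisation**, by adding INJURY or FAILURE at randomisation (on creatinine or urine output) to the exclusions. The outcome, the 60% and 40% rates and the 214 then all refer to the same patients. The cost is one eligibility line and slower recruitment at a single unit. The size of that delay is unknown because the share affected is unknown.
2. **Alternative: define the primary outcome as at least one RIFLE class worse than the class at randomisation, and exclude FAILURE at randomisation.** This keeps INJURY patients. It takes more than an endpoint sentence, because 60% versus 40% is framed for patients starting in RISK and would have to be re-justified for a mixed population, with the sample size recalculated if the rates change.

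Either choice should be made while allocation is still blinded.

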**Figure 2 F2:**
[figure not shown]
**Overview of the SPARK study drug infusion algorithm**.

The study infusion bag will contain 2000 mg of furosemide in 500 mL of 0.9%NaCl for a final concentration of 4 mg/mL. The appearance of the study infusion bags for furosemide and placebo will be identical and there will be no marking on the infusion bags other than a 4-digit coded identifying study number. This will minimize bias and ensure blinding of allocation by the study investigators, research coordinator, ICU physicians and all involved health care providers.

The continuous infusion will be titrated to achieve a target urine output in the range of 1.0-2.0 mL/kg/hr. The treatment algorithm for titration of the continuous infusion is shown in Figure 2. Each patient will be administered a loading dose of 0.4 mg/kg as a separate infusion bag followed by a continuous infusion commenced at a dose of 0.05 mg/kg/hr (Table 1). The maximum infusion rate will be 0.40 mg/kg/hr. The urine output will be assessed hourly. If the target urine output has been achieved, then the current infusion rate will be continued. If the target urine output has not been achieved, the dose will be increased to the next infusion rate in the algorithm. If the urine output is too brisk (>2 mL/kg/hr x 2 hrs), the infusion rate will be reduced. If the urine output is still >2 mL/kg/hr AND the infusion rate is at the lowest rate, the study drug will be discontinued infusion until the urine output is <1 mL/kg/hr. If any of the following criteria are fulfilled: decrease in mean arterial pressure <65 AND/OR addition of or an increase in vasoactive requirements of ≥20% to achieve goal mean arterial pressure OR central venous pressure <8 cmH2O OR central venous oxygen saturation <60% OR a cardiac index <2.0 L/min/1.73 m^2 ^(if measured) at any time, the consultant ICU physician and ICU team will be notified to review the patient.

**Table 1 T1:** Summary of weight-based categories for commencement for study infusion rate (concentration study drug 4 mg/mL)

Weight Category (kg)	Bolus loading dose	Start infusion dose	Start infusion dose (mg/hr)	Start infusion rate (mL/hr)
≤50	0.4 mg/kg	0.05 mg/kg/hr	2.5	0.6

55	0.4 mg/kg	0.05 mg/kg/hr	2.8	0.7

60	0.4 mg/kg	0.05 mg/kg/hr	3.0	0.8

65	0.4 mg/kg	0.05 mg/kg/hr	3.3	0.8

70	0.4 mg/kg	0.05 mg/kg/hr	3.5	0.9

75	0.4 mg/kg	0.05 mg/kg/hr	3.8	0.9

80	0.4 mg/kg	0.05 mg/kg/hr	4.0	1.0

85	0.4 mg/kg	0.05 mg/kg/hr	4.3	1.1

90	0.4 mg/kg	0.05 mg/kg/hr	4.5	1.1

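### The primary endpoint can be met on urine output alone while the drug is titrated to urine output, so a lower event rate need not mean less kidney injury

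*Protocol article*

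**What the plan says.** **Endpoint.** Under Sample Size Estimation the primary outcome is "progression in AKI to the development of either RIFLE class" Injury or Failure, starting from Risk.

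**Class definitions.** Under Operational Definitions, Acute kidney injury (AKI), each class has a creatinine route and a urine-output route joined by *or*:
- Risk (entry), urine route: "a reduction in urine output of ≤ 0.5 mL/kg/hr for ≥ 6 hours".
- Injury: creatinine at least 2.0-fold, or "a reduction in urine output of ≤ 0.5 mL/kg/hr for ≥ 12 hours".
- Failure, urine route: "a reduction in urine output of ≤0.3 mL/kg/hr for ≥ 24 hours or anuria for ≥ 12 hours".

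**Intervention.** Under Study Intervention: "The continuous infusion will be titrated to achieve a target urine output in the range of 1.0-2.0 mL/kg/hr". Output is checked every hour and the rate is stepped up, to a maximum, while the target is not met.

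**Evidence cited.** The Background reports from a systematic review of loop diuretics "a greater increase in urine output from baseline (OR, 2.6, p = 0.004") and no statistical difference in mortality (OR 1.28, p = 0.18) or renal recovery (OR 0.88, p = 0.5). It also reports a shorter time to creatinine decline (-2.1 days, p = 0.01) and a shorter duration of RRT (-1.4 days, p = 0.02).

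**Analysis.** Statistical Analysis compares the proportion progressing by Fisher's exact test. The article does not limit progression to creatinine or describe a breakdown by criterion, and Potential Challenges with the Trial does not discuss the overlap.

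**The concern.** The Background hypothesis is that timely furosemide attenuates the injury itself, through lower tubular oxygen demand and less apoptosis. The endpoint is meant to measure that. But a diuretic acts directly on one of the two routes by which an event is scored. A furosemide patient whose output is held at target does not meet the urine criterion while it is held there, whatever the creatinine does. A placebo patient is titrated by the same algorithm, but with saline.

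Entry on oliguria makes this sharper. Risk and Injury share the 0.5 mL/kg/hr threshold and differ only in duration, so a patient who enters at 6 hours becomes an event after 12 - 6 = 6 more hours of unchanged output.

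Randomization and blinding do not remove the problem, because the difference arises from the drug's pharmacology and not from selection or ascertainment. What is at stake is interpretation. A significant primary result could reflect less kidney injury, more urine, or both, and the Discussion intends the trial to inform a phase III design.

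**Working it through.** **1. The plan's own figure.** Inputs from Sample Size Estimation: 60% vs 40%, two-sided alpha 0.05, power 80%.

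n per arm = [1.960 × √(2 × 0.5 × 0.5) + 0.842 × √(0.6 × 0.4 + 0.4 × 0.6)]² / 0.20² = (1.386 + 0.583)² / 0.04 = 96.9.

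Continuity correction: (96.9 / 4) × [1 + √(1 + 4 / (96.9 × 0.20))]² = 106.7, so 107 per arm and 214 in total. This matches. With 216 patients (108 per arm, inferring 1:1 allocation), exact Fisher power is 80.2%. The sample-size arithmetic is not in question.

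**2. Diuresis alone.** Suppose furosemide has no effect on creatinine-defined progression. Let *a* be the control percentage points reached by urine output only, and *s* the fraction of those averted by diuresis. Then the furosemide rate = 60 - a × s. Neither *a* nor *s* is in the document. Assumed ranges: a = 15 to 30, s = 50% to 70%. Probabilities are exact, from the two-sided Fisher test at 0.05 with 108 per arm, counting only results that favour furosemide.

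| a (points) | s | a × s | Rates (%) | Chance of a significant result for furosemide |
|---|---|---|---|---|
| 0 | any | 0 | 60 vs 60 | 1.8% |
| 15 | 50% | 7.5 | 60 vs 52.5 | 16% |
| 15 | 70% | 10.5 | 60 vs 49.5 | 29% |
| 30 | 50% | 15 | 60 vs 45 | 54% |
| 30 | 70% | 21 | 60 vs 39 | 84% |

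The right comparator is the first row: 1.8% in the favourable direction (2.5% nominal), not 5%. The whole planned 20-point effect would come from diuresis when a × s = 20, that is, when one third of control events (20/60) are averted urine-only events.

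**3. What a creatinine-only analysis could detect.** The same range of *a* leaves a creatinine control rate of 60 - 15 = 45% down to 60 - 30 = 30%. The planned relative reduction is 20/60 = one third, giving 45 vs 30% and 30 vs 20%. Exact Fisher power at 108 per arm is 58% and 34%.

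For 80% power by the formula in step 1, the totals would be:
- 45 vs 30%: 352 patients.
- 30 vs 20%: 626 patients.

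Power holds up only if the absolute 20 points are kept on creatinine (82% at 50 vs 30%, 87% at 40 vs 20%). That presumes a larger relative effect than planned: 40% and 50% instead of 33%.

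**The case against.** **RIFLE is a deliberate choice.** Potential Challenges with the Trial defends it as a validated consensus classification, and the Background cites small trials suggesting that conversion from oliguric to non-oliguric AKI may itself reduce severity. This stands as a reason to keep full RIFLE as primary. It does not answer the point, because validity as a classification does not carry over to a trial whose drug drives one of the criteria.

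**Other outcomes are planned.** RRT, recovery and mortality are secondary, injury biomarkers are tertiary, and the Discussion leaves RRT or mortality to phase III. So a phase III decision would not rest on the primary result alone. But renal recovery and the first RRT criterion themselves use urine output. A breakdown by criterion may also exist in an analysis plan that is not shown. The point rests on the endpoint as the article fixes it, not on the lack of that analysis.

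**Stronger readings that the document does not support:**
- *The cited review shows diuresis without renal benefit.* It also reports faster creatinine decline and shorter RRT, and the Background calls the evidence poor, with late treatment and large boluses. It does not settle the question.
- *Most events will be urine-only.* No figure for that share is given.
- *Responders cannot have a urine-output event.* This holds only while output is sustained. The rate is capped, the infusion can be paused, and it ends at ICU discharge or after 7 days. Urgent furosemide is allowed in any enrolled patient.
- *The type I error is inflated.* On the endpoint as defined, the arms would truly differ. The fault lies in what the difference can be taken to mean.

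**Conclusion.** The point holds as one of interpretation. By the protocol's own definitions, furosemide can lower the primary event rate by raising urine output, and the stated analysis cannot tell this from less kidney injury. With no creatinine effect, the chance of a significant result in its favour is about 16% to 84%, against about 1.8% for an inert drug. That range rests wholly on the assumed 15 to 30 urine-only points and 50-70% averted. It shows that the effect could be large, not that it will be. Events reached by creatinine still count in both arms, so the distortion is confined to urine-only events.

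A reader might infer that the primary endpoint must be replaced. The document does not force that: replacement costs power or sample size and is a trade-off for the sponsor. This is a cheap improvement to the analysis and to the claim.

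**What to change.** 1. Keep full RIFLE as the primary if wished, but record for each event which criterion triggered it: creatinine, urine output, or both.
2. Prespecify progression by the RIFLE creatinine criteria alone as a key secondary analysis.
3. Add a sensitivity analysis that counts RRT as an event except when it was started only for oliguria. Counting all RRT would bring urine output back in through the first RRT criterion (under 100 mL in 4 hours).
4. Add a sensitivity analysis that corrects creatinine for cumulative fluid balance, since the drug changes that balance.
5. State that reduced kidney injury will not be claimed unless the creatinine-based result agrees.

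**Cost.** Creatinine, urine output and fluid balance are already collected daily, so the work is a little more coding and analysis. The claim becomes stricter, and the creatinine analysis has lower power at the planned one-third reduction (about 58% at 45 vs 30%, 34% at 30 vs 20%), which should be stated in advance. If the sponsor instead makes creatinine the primary, this is more than a change of wording: the 60% rate and the 80% power must be re-derived. No change to dosing or titration is implied.
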